### Statistical analyses

Standard methods for the analysis of randomized controlled trials will be employed. Firstly a comparison of baseline characteristics of the two groups will be compared for demographics, primary and secondary outcome measures. Though our starting hypothesis called from a superiority of RAGT with respect to CT, to allow for the chance that participants enrolled in the CT group could have better outcomes than those in the intervention arm, we will use two-tailed tests of significance for all analyses. A *p* value of 0.05 will be considered statistically significant.

For the primary hypothesis, a two-way repeated measure analysis of variance (factors: treatment, time) will be run to compare differences in gait speed within the RAGT and CT groups at baseline, after treatment and follow-up. Given the large number of planned secondary outcomes, in order to reduce the probability of a false positive result, for these specific analyses the significance level will be fixed at 0.01.

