
### Aims

The primary objective of the study is the verification of the starting hypothesis that RAGT could have greater benefit, compared with conventional therapy alone, in gait speed improvement as assessed by the Timed 25-Foot Walk Test (T25FW).

Secondarily, the study aims to determine whether fatigue, QoL, balance and mobility are improved by RAGT. Finally, the study aims to collect information on whether RAGT or the active control group (CT) influence markers of plasticity, including clinical and circulating biomarkers, and if these modifications are correlated with clinical outcome. The ultimate goal is to draw tailored rehabilitation strategies capable of bypassing the person-specific treatment response in MS patients.

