### Concomitant care and recommendations

During the 4-week period of in-hospital training, patients will be asked not to undertake other physiotherapist treatments. Moreover, patients will be asked to wear the same shoes and orthosis during all the testing and training sessions.

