### Sample size and power

The primary outcome for this study is to detect walking differences (specifically, T25FW measurement) between MS subjects who underwent RAGT and MS subjects who underwent CT. To calculate the sample size for this study, we used the data from a previous study [18] where a RAGT effect size of 0.40 was observed. This value is based on a decrease of values for T25FW from 8.8 ± 3.1 s at baseline to 7.4 ± 3.8 s after RAGT. Given equal allocation between treatment and control arms, 88 subjects are required to maintain a Type I error rate of 5.0 and 80% power to detect a difference between intervention groups. Conservatively, we expect a 10% rate of dropout or loss to follow-up. We will assume that dropout participants will not improve from the last measured point; thus, the sample size will be increased by 10% to 98 subjects (49 per arm).

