### Additional statistical analysis

The statistical significance of primary and secondary outcome measures in score change between the groups will be assessed using *t* tests for symmetrically distributed data and analogous nonparametric tests, such as the Wilcoxon signed-rank test, for data that are skewed. If a statistically different distribution between the two groups in the baseline outcome level is identified, a secondary analysis that employs a multivariate modeling, such as analysis of covariance, to adjust for these factors, will be performed. Since MS encompass a wide spectrum of disabilities, the general linear model will also analyze the effect of several factors, so we will conduct exploratory analyses in which we will include the MS onset (year) and EDSS subscores (pyramidal function, cerebellar function and sensitive functions) which define our MS in the model. Furthermore, the possible effects of disease-modifying or symptom-modifying drugs (i.e., fampridine) on motor outcome will be explored. Permutation tests may be implemented to verify that valid *p* values will be obtained even if model assumptions are not correct. Analysis of hemodynamic, metabolic and laboratory-based measures will be performed according to the procedures detailed above. Possible correlation between these factors and clinical measures will be assessed by Spearman’s rho or included in multiple regression models.

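### The primary repeated-measures ANOVA is worded as a within-group comparison and names no between-arm term or time point as the primary test, although the question is RAGT versus CT

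*Protocol article*

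**What the plan says.** The Aims section of the protocol article states the primary hypothesis as a comparison of arms: "RAGT could have greater benefit, compared with conventional therapy alone, in gait speed improvement". The Sample size and power section repeats this, framing the primary outcome as a walking difference "between MS subjects who underwent RAGT and MS subjects who underwent CT".

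For that hypothesis, the Statistical analyses section specifies a "two-way repeated measure analysis of variance (factors: treatment, time) will be run to compare differences in gait speed within the RAGT and CT groups". The time factor has three levels: the visit before training (T0), the end of treatment (T2) and the three-month visit (T3). Baseline is therefore a level of the outcome. The section does not say which of the three F tests (treatment, time, treatment by time) decides the hypothesis, or at which visit.

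Under Additional statistical analysis the article adds a direct comparison of arms: "The statistical significance of primary and secondary outcome measures in score change between the groups will be assessed", by t test or a nonparametric analogue. The same section allows analysis of covariance only as a secondary analysis, and only when a statistically detectable baseline difference is found.

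**The concern.** The stated purpose of the primary analysis does not match the primary question. The ANOVA can be read in three ways:

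- **Within-arm change.** This is the literal wording. A significant change in one arm and not in the other is not evidence that the arms differ.
- **Treatment main effect.** This averages the arm difference over all three visits. Randomisation leaves no treatment effect at baseline, so that visit only dilutes the average.
- **Treatment-by-time interaction.** This does compare the arms. With three visits it is a 2-degree-of-freedom test, and rejection does not show whether the arms differ at T2, at T3 or at both.

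T2 and T3 are different questions. T3 falls three months after training ends, and the limit on outside physiotherapy covers only the training weeks: "During the 4-week period of in-hospital training, patients will be asked not to undertake other physiotherapist treatments".

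At stake is the trial's one confirmatory claim. The test that supports it could be chosen after the data are seen, and the possible choices differ widely in power. Making baseline adjustment depend on a baseline significance test adds a second data-driven choice and gives up precision when that test is not significant.

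**Working it through.** **Inputs from the document.** There are 88 evaluable patients, 44 per arm, with a two-sided 5% test and an effect size of 0.40. The 0.40 reproduces from the quoted T25FW values: (8.8 − 7.4)/√((3.1² + 3.8²)/2) = 1.4/3.47 = 0.404. It is a pre-post change in one arm. The dropout step also reproduces: 88/0.9 = 97.8, rounded up to 98.

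**Assumptions.** The between-arm difference is 0.40 SD at T2. At T3 it is 0.40 (kept), 0.20 (halved) or 0 (gone). SD is equal at all visits, with one common correlation r between visits. The document gives no r, so 0.5 to 0.9 is shown.

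**Formulas** (noncentral F, N = 88, N/4 = 22; effects at baseline, T2 and T3 are 0, 0.40 and the T3 value):

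- Main effect: λ = 22 × (mean effect)² / [(1 + 2r)/3], on 1 and 86 df.
- Interaction: λ = 22 × (sum of squared deviations of the three effects from their mean) / (1 − r), on 2 and 172 df.
- T2 difference adjusted for baseline: λ = 22 × 0.40² / (1 − r²), on 1 and 85 df.

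**Example, r = 0.7, effect kept.** The mean effect is 0.80/3 = 0.267, so the main-effect λ = 22 × 0.0711/0.80 = 1.96, power 28%. The squared deviations sum to 0.1067, so the interaction λ = 22 × 0.1067/0.30 = 7.82, power 70%. The adjusted T2 difference has λ = 22 × 0.16/0.51 = 6.90, power 74%.

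**If the effect is halved at T3,** the mean effect is 0.20 and the squared deviations sum to 0.08. **If it is gone,** the mean effect is 0.133 and the sum is again 0.1067. The interaction therefore has the same power whether the effect persists in full or disappears.

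| Test | Effect at T3 | r = 0.5 | r = 0.7 | r = 0.8 | r = 0.9 |
|---|---|---|---|---|---|
| Main effect | kept | 33% | 28% | 26% | 25% |
| Main effect | halved | 21% | 18% | 17% | 16% |
| Main effect | gone | 12% | 11% | 10% | 10% |
| Interaction, 2 df | kept or gone | 47% | 70% | 87% | 99% |
| Interaction, 2 df | halved | 37% | 57% | 75% | 97% |
| T2 difference, baseline-adjusted | any | 57% | 74% | 87% | 99% |

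A simulation of 4,000 trials per setting, covering the kept and gone cases, agrees to within about 2 percentage points.

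**Literal within-arm reading.** Suppose both arms improve equally, by 0.4 SD, so there is no arm difference. A paired test in one arm has noncentrality 0.4√44/√(2(1 − r)), which gives power p of 74%, 92% and 98% at r = 0.5, 0.7 and 0.8. The chance that exactly one arm is significant is 2p(1 − p): 39%, 15% and 3%. At r = 0.9 it is practically nil.

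**The case against.** The strongest reply is that a model with treatment and time as factors is not a within-arm analysis. Its interaction tests differential change between arms, which is what the Aims ask. The Aims, the sample-size section and the stated hypothesis of superiority all point to a between-arm intention, so the word within may be loose drafting. The interaction also costs little power when the effect is fully kept or fully gone: 70% against 74% at r = 0.7, and level at 0.8 and above. The choice of decisive term could also be in an analysis plan that is not shown.

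Much of this stands. A reader might infer that the planned model cannot test RAGT against CT; that is too strong. What remains is that the article does more than omit a detail. It states a purpose for the primary test, and that purpose does not match the objective.

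Four other inferences are tempting but not supported:

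- **Patients with a missed visit are lost from the ANOVA.** The Intention-to-treat section plans multiple imputation.
- **The ANOVA and the t tests of change are unranked.** The ANOVA is assigned to the primary hypothesis, and the t tests stand under a heading that marks them as additional.
- **Leaving the intermediate visit (T1) out is an error.** It is a mid-treatment measurement, and omitting it from the primary model is a legitimate choice.
- **The same data would give opposite conclusions under different readings.** The calculations show different power, and a false lead under the within-arm reading. They do not show a reversal of results.

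**Conclusion.** The concern holds as a misworded and undesignated primary test. It does not hold as a claim that the model is incapable of a between-arm comparison.

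The size depends on the reading. The main effect would leave power at or below 33% in every case shown. The interaction loses up to 10 percentage points against the adjusted T2 difference if the effect is kept or gone, and 2 to 20 points if it halves by T3; in no case does it say when the arms differ. Within-arm testing could suggest superiority where none exists in up to about 39% of trials, under equal improvement of 0.4 SD in both arms.

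These figures rest on an assumed correlation, on equal variances and correlations across visits, and on treating 0.40 as a between-arm difference although the article derives it from one arm's pre-post change. They compare the tests with one another and do not forecast the trial's power. Whether 88 patients follow from 0.40 is a separate matter. The mismatch of wording and question needs none of these assumptions.

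**What to change.** State one primary test: the RAGT minus CT difference in gait speed at T2, two-sided 5%, adjusted for baseline gait speed and EDSS stratum (the randomisation stratification factor) in all patients. Use ANCOVA, or a mixed model with baseline as a covariate rather than an outcome level, with the multiple imputation already planned.

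Then:

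- make the T3 difference a secondary outcome at the 0.01 level that the article already sets for secondary outcomes;
- report within-arm changes descriptively;
- remove the baseline significance test as the trigger for adjustment.

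The cost is wording only. The data are already being collected, and the article gives the trial status as recruiting, so the test can be fixed before the final analysis. The downside is that T3 no longer counts toward the primary claim.

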### Additional statistical analysis

The statistical significance of primary and secondary outcome measures in score change between the groups will be assessed using *t* tests for symmetrically distributed data and analogous nonparametric tests, such as the Wilcoxon signed-rank test, for data that are skewed. If a statistically different distribution between the two groups in the baseline outcome level is identified, a secondary analysis that employs a multivariate modeling, such as analysis of covariance, to adjust for these factors, will be performed. Since MS encompass a wide spectrum of disabilities, the general linear model will also analyze the effect of several factors, so we will conduct exploratory analyses in which we will include the MS onset (year) and EDSS subscores (pyramidal function, cerebellar function and sensitive functions) which define our MS in the model. Furthermore, the possible effects of disease-modifying or symptom-modifying drugs (i.e., fampridine) on motor outcome will be explored. Permutation tests may be implemented to verify that valid *p* values will be obtained even if model assumptions are not correct. Analysis of hemodynamic, metabolic and laboratory-based measures will be performed according to the procedures detailed above. Possible correlation between these factors and clinical measures will be assessed by Spearman’s rho or included in multiple regression models.

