## Methods

### Study design and setting

This study is a parallel-assignment, single-blinded, randomized controlled trial with the assessor blinded to the group allocation of participants (Fig. 1). Participants meeting the inclusion criteria and who provide written informed consent will be randomly assigned to one of the two treatments: the RAGT or the CT group. This study was approved by the Ethics Committee of Ferrara province with approval number 101-2012. This protocol is reported following the Standard Protocol Items: Recommendations for Interventional Trials (SPIRIT) guidelines [52]. A populated SPIRIT Checklist is available as additional file (Additional file 1). Subjects will be recruited using several methods, including the identification of MS patients who are referred to the Rehabilitation Clinics of the Operative Unit of Physical and Rehabilitation Medicine of Ferrara University Hospital and from the Centro Malattie Rare e Neuroimmunitarie, IRCCS Neuroscienze Bellaria, Bologna. All the interventions scheduled, as well as the outcome measure assessment, will be performed at the Operative Unit of Physical and Rehabilitation Medicine of Ferrara University Hospital.

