### Randomization and blinding

After the collection of the informed consent and of the baseline data, the physician responsible for the enrollment will create the allocation sequence, on a personal password-protected computer. The password to log into the allocation list will be given only to the research coordinator, to the physician who created it, and to the administrator responsible of randomization. Then patients will be randomized to one of the two groups by the external administrator not involved in the trial to prevent selection bias through a computerized randomization stratification approach. Participants will be stratified by their degree of impairment (EDSS score) to obtain a balance between groups regarding the baseline physical capacity. The randomization scheme (1:1 ratio) will be set up in permuted blocks of 4 to ensure a similar number of participants between groups. Finally, the subjects will be assigned to one of the two treatment groups: RAGT (experimental group) or CT (active control group). The participants cannot be blinded to the two interventions as the two training protocols were detailed in the informative form for the patients given during the screening visit. Once randomized, patients cannot change the treatment assigned for any reason (e.g., participant request), but in case any medical conditions derived from that specific treatment develop, the training will be immediately suspended. Outcome measure assessors who have to remain blind to group allocation will not have access to the randomization list. Unblinding will not be permissible for these researchers. All outcome data will be recorded on two different electronic spreadsheets by two blinded researchers involved in the trial, and the accuracy of the data will be checked by the research coordinator for all the outcome measures. The privacy of the participants and their personal medical records will be guaranteed by treating the data according to the Italian Law n. 196/2003, to the “Safe Harbor Act” (2000/520/CE) and to the “European Union Data Protection Directive (95/46/EC 24 October 1995).”

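### The nonparametric test named for comparing skewed change scores between the arms is the Wilcoxon signed-rank test, which cannot compare two independent groups

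*Protocol article*

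**What the plan says.** The first sentence of Additional statistical analysis sets the comparison: "The statistical significance of primary and secondary outcome measures in score change between the groups will be assessed". For symmetric data the method is the t test. For the rest it is "analogous nonparametric tests, such as the Wilcoxon signed-rank test, for data that are skewed". No rank-sum or Mann-Whitney test is named anywhere in the article.

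The arms are independent. Study design and setting states: "This study is a parallel-assignment, single-blinded, randomized controlled trial with the assessor blinded to the group allocation of participants". Randomization and blinding adds stratification by EDSS score and says: "The randomization scheme (1:1 ratio) will be set up in permuted blocks of 4". Neither section matches a RAGT patient to a CT patient.

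Two other provisions matter here. Statistical analyses assigns the primary hypothesis to a two-way repeated-measures analysis of variance with factors treatment and time. It also sets two-sided testing, a general level of 0.05, and a stricter level of 0.01 for secondary outcomes.

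**The concern.** The sentence asks whether change differs between RAGT and CT. The one nonparametric test that it names answers another question: whether a single set of differences is centred on zero. An analyst who follows the text has two options, and neither gives the comparison.

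- Apply the test inside each arm. The result is two tests of change from baseline.
- Apply it across arms. Patients must then be paired by some rule that the design does not supply.

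The sentence covers the primary and secondary outcomes whenever their changes are skewed. The article does not say how often that will be. It is an assumption, though a plausible one for timed walking and plasma markers, and the authors plan for it themselves.

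**Working it through.** The article states no figure on this point, so there is none to reproduce. The check sets the test against the design and then uses simulation to show what each literal reading does.

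**1. Structure.** Let D be a patient's change score. The stated question concerns the distribution of D in RAGT against that in CT, with up to 49 patients per arm. The signed-rank test takes one list of differences and tests symmetry about zero. It has no term for arm.

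**2. Read across arms.**
- With 49 and 48 patients, the two-sample call fails because pairs are required.
- With 49 and 49, it runs only on arbitrary pairs. One simulated skewed data set (log-normal, log-scale means 0 and 0.5, log-scale SD 1) was paired at random 2,000 times. The p value ran from 0.00002 to 0.061. The rank-sum test gives a single value, 0.0043.

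**3. Read within arms.** Both arms were given the same true improvement of 0.4 SD of change: 49 per arm, normal changes, 2,000 runs, level 0.05.
- Signed-rank within one arm was significant in 76% of runs.
- Exactly one of the two arms was significant in 34.5% of runs.
- Rank-sum between arms was significant in 4.3% of runs, close to the nominal 5%.

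**4. What misuse could cost.** Suppose the within-arm results were read as a comparison. With q the probability that one arm is significant, and equal true improvement in both arms, the chance that RAGT is significant and CT is not is q(1 − q). This cannot exceed 0.5 × 0.5 = 0.25. The table uses 44 per arm, half of the 88 in Sample size and power.

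| Shape of change | Common improvement (SD of change) | Level | q | q(1 − q) |
|---|---|---|---|---|
| Normal | 0.30 | 0.05 | 0.47 | 0.25 |
| Normal | 0.40 | 0.05 | 0.72 | 0.20 |
| Normal | 0.61 | 0.05 | 0.97 | 0.03 |
| Normal | 0.30 | 0.01 | 0.24 | 0.18 |
| Normal | 0.40 | 0.01 | 0.47 | 0.25 |
| Log-normal, long tail towards improvement | 0.30 | 0.05 | 0.20 | 0.16 |
| Log-normal, long tail towards improvement | 0.40 | 0.05 | 0.60 | 0.24 |
| Log-normal, long tail towards worsening | 0.30 | 0.05 | 0.89 | 0.10 |
| Log-normal, long tail towards worsening | 0.40 | 0.05 | 0.96 | 0.04 |

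The log-normal rows use log-scale SD 0.8, which is an assumption.

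**5. Why the improvement is also an assumption.** The effect size of 0.40 in Sample size and power is scaled by the SD of scores: (8.8 − 7.4)/√((3.1² + 3.8²)/2) = 1.4/3.47 = 0.40. The SD of change depends on the correlation r between the two measurements, which the article does not give: √(3.1² + 3.8² − 2r × 3.1 × 3.8).
- r = 0.5: √(24.05 − 11.78) = 3.50, and 1.4/3.50 = 0.40.
- r = 0.8: √(24.05 − 18.85) = 2.28, and 1.4/2.28 = 0.61.

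**The case against.** The strongest reply is that the test is only an example. The class is defined as nonparametric analogues of a t test on change between groups, and for two groups that is the rank-sum test. A statistician will run the analysis, the paired call fails when the arms differ in size, and the same section allows permutation tests. On this view it is a slip of one word.

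Part of this stands. The intended comparison is stated correctly, and the authors may well have meant the rank-sum test. But the only example given is invalid for that comparison. The paired call does run when the arms are equal in size. The permutation tests are optional and serve as a check on model assumptions, so they do not replace the named test.

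A reader might infer more: that the primary result is compromised, or that the plan carries a false-positive rate of about 20% for RAGT alone and 40% for either arm alone. The article does not support this.
- The primary hypothesis has its own analysis, which this sentence leaves untouched. The wording there about gait speed within the groups describes a model with a treatment factor.
- The article nowhere says that a significant result in one arm only will be taken as superiority.
- Those rates come from normal changes, although the test is reserved for skewed data, and from level 0.05, although secondary outcomes are tested at 0.01.

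Nor does the sentence govern every secondary analysis: the cortical activation maps have their own t test comparison under Cerebral activation analysis during a motor task.

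**Conclusion.** The point holds as an error in the named test. The signed-rank test cannot make the between-group comparison for which it is specified, and nothing else in the article corrects it. It affects the additional between-group analyses of skewed outcomes and leaves the primary repeated-measures analysis of variance as it is.

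The inconsistency with the design needs no assumption. The size of any harm does. If within-arm results were read as a comparison, illustrative rates of a false RAGT-only finding run from about 3% to 25%, depending on the common improvement, the direction and degree of skewness, and the level of 0.05 or 0.01. No single figure in that range can be attributed to the plan. This is a small correction that should be made before the data are analysed.

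**What to change.** In Additional statistical analysis, replace the Wilcoxon signed-rank test with the Wilcoxon rank-sum (Mann-Whitney) test, applied to the change scores of the two arms. If a separate statistical analysis plan repeats the wording, make the same change there.

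Stratifying the rank-sum test by EDSS stratum (van Elteren), to match the stratified randomisation, is an optional refinement that the error itself does not require.

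The cost is one term. Sample size, visits, data collection and the primary analysis do not change.

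### Baseline-adjusted analysis is only a secondary step triggered by a significance test, and neither baseline T25FW nor the EDSS stratum is a covariate in the primary model; the cost is small to moderate and the fix is nearly free

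*Protocol article*

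**What the plan says.** All references are to the protocol article.

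- **Statistical analyses.** The primary hypothesis is tested by a repeated-measures ANOVA with treatment and time as its two factors. Baseline is one of the time points. The section also announces that a "comparison of baseline characteristics of the two groups will be compared", covering demographics and the primary and secondary outcomes.
- **Additional statistical analysis.** Score changes are compared between arms by t test or a nonparametric test. ANCOVA is reserved for one circumstance: "If a statistically different distribution between the two groups in the baseline outcome level is identified, a secondary analysis that employs a multivariate modeling" is then performed. EDSS subscores appear only in exploratory models.
- **Randomization and blinding.** "Participants will be stratified by their degree of impairment (EDSS score"), with the stated purpose of balancing baseline physical capacity. The section adds: "The randomization scheme (1:1 ratio) will be set up in permuted blocks of 4".

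These choices are stated in the article, so they are not details left to an analysis plan that is not shown.

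**The concern.** Under sound randomisation, a baseline difference is a chance event and its p-value does not show whether adjustment is worthwhile. That depends on how strongly the covariate predicts the outcome, and baseline T25FW is an obvious predictor of later T25FW. Making ANCOVA depend on the test has three consequences:

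1. In most trials the more precise estimator is never computed.
2. A prognostic imbalance that just misses significance goes uncorrected, apart from the subtraction of baseline.
3. If the test is positive, the trial reports an unadjusted primary result and an adjusted secondary result, and no rule says which one governs the conclusion.

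The EDSS stratum was judged prognostic enough to constrain the randomisation, yet it is in no confirmatory model. At stake are some precision and a clear single answer. The validity of the test is not at stake.

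**Working it through.** **Inputs.** From Sample size and power: T25FW "from 8.8 ± 3.1 s at baseline to 7.4 ± 3.8 s after RAGT", so s0 = 3.1 s, s1 = 3.8 s and difference 1.4 s; 88 evaluable (44 per arm) and 98 randomised (49 per arm). From Statistical analyses: "we will use two-tailed tests of significance for all analyses". The correlation r between baseline and post-treatment T25FW is not given; I assume 0.5 to 0.9. I take the treatment-by-time contrast as the primary test and treat it as a comparison of changes between two visits.

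**The plan's own figures.** The effect size reproduces: pooled SD = √[(3.1² + 3.8²)/2] = 3.47 and 1.4/3.47 = 0.404, against "where a RAGT effect size of 0.40 was observed". The sample size, "88 subjects are required to maintain a Type I error rate of 5.0 and 80% power", does not. A two-group comparison at 0.40 needs 99 per arm (198). With equal SDs, 88 fits 0.40 only if r is about 0.74 (ANCOVA) or 0.78 (change score). That is a separate matter, but it shows there is little precision to spare.

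**Variance, with the article's SDs.**

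- Change score: s0² + s1² − 2·r·s0·s1
- ANCOVA: s1²(1 − r²)
- Example at r = 0.5: change 24.05 − 11.78 = 12.27; ANCOVA 14.44 × 0.75 = 10.83; ratio 0.88

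**Conditional shift.**

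- Largest non-significant baseline difference at 49 per arm: 1.985 × √(2/49) = 0.401 SD, and 0.401 × 3.1 = 1.24 s.
- Given that imbalance, the expected error in the change-score difference is (r × 3.8/3.1 − 1) × 1.24 s.
- Example at r = 0.5: (0.613 − 1) × 1.24 = −0.48 s.

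| r | ANCOVA/change variance | Power for 1.4 s, 44 per arm: change v ANCOVA | Shift at 1.24 s imbalance |
|---|---|---|---|
| 0.5 | 0.88 | 46.6% v 51.4% | −0.48 s |
| 0.6 | 0.93 | 55.0% v 57.9% | −0.33 s |
| 0.7 | 0.97 | 66.6% v 67.7% | −0.18 s |
| 0.8 | 1.00 | 82.1% v 82.1% | −0.02 s |
| 0.9 | 0.96 | 97.3% v 97.7% | +0.13 s |

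A negative shift means that the arm starting slower appears to improve more than it truly does. The two methods coincide when r × 3.8/3.1 = 1, that is at r = 0.82.

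**Equal SDs.** The ratio is (1 − r²)/[2(1 − r)] = (1 + r)/2, which runs from 0.75 to 0.95. Power at an effect size of 0.40 with 44 per arm is 47% v 58% (r = 0.5), 68% v 75% (r = 0.7) and 84% v 88% (r = 0.8).

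**Error rates.** These come from 20,000 simulated null trials per setting, 49 per arm, equal SDs.

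- Overall type I error of the change-score test: 0.050.
- Among trials with a moderate but non-significant baseline difference (|t| between 1.5 and 1.98): change score 0.107 at r = 0.5 and 0.072 at r = 0.8; ANCOVA about 0.05.
- With a stratum assumed to explain 20% of variance: change score 0.048 to 0.049; ANCOVA without the stratum 0.042 to 0.047; ANCOVA with baseline and stratum 0.050.

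**The case against.** The strongest reply is that little is lost.

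- **Baseline is used.** A reader might infer that the best predictor is ignored unless the test is positive. That is wrong: baseline is a level of time in the ANOVA, and the additional tests are on score change. No comparison of post-treatment values alone is planned, so the larger bias and precision loss of such an analysis do not apply.
- **The trigger does not choose the primary analysis.** The triggered ANCOVA is labelled secondary. Even if the test did choose between change score and ANCOVA, the simulated overall error is 0.046 to 0.047 (no stratum effect).
- **Leaving out the stratum hardly matters for a change score.** A reader might infer that standard errors are materially too large for the stratified design. A stratum effect that is the same at both visits cancels in the within-patient contrast, and the simulated error is almost nominal.
- **A 1.24 s imbalance is the extreme edge of non-significance.** Stratifying by EDSS makes it rarer if EDSS is related to gait speed.
- **The equal-SD gains overstate the case.** The article's SDs give less, and almost nothing near r = 0.8.

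All of this stands and limits the size of the point. It does not defend the rule itself: a significance test is still the wrong criterion for adjustment, and two competing results can still arise.

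**Conclusion.** The point holds as one of efficiency and clarity. The article ties ANCOVA to a baseline significance test and keeps baseline T25FW and the EDSS stratum out of the primary model as covariates. Against prespecified ANCOVA, the change-score approach gives up about 0 to 12% of variance with the article's SDs, which is at most about 5 points of power, or 5 to 25% if the SDs are equal. An imbalance of 1.24 s that goes unadjusted shifts the difference by about 0.02 to 0.5 s, depending on r, against 1.4 s.

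A reader might go further and infer a biased primary estimate or an inflated type I error. The documents do not support that: the shift is conditional on the imbalance that happens to occur, while over all randomisations the estimate is unbiased and the error rate nominal.

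The sizes rest on the assumed range of r and on reading the primary test as the treatment-by-time contrast. They also take SDs from one treated group in an earlier study as valid for both arms. Because r is not in the documents, the loss cannot be fixed more closely.

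**What to change.** 1. Prespecify the primary between-arm estimate as ANCOVA or a mixed model for post-baseline T25FW, with baseline T25FW and EDSS stratum as covariates whatever the observed balance. Define the stratum as it was used in the randomisation.
2. Do the same for continuous clinical secondary outcomes, each with its own baseline value. Where data are skewed, use a transformed or rank-based ANCOVA, so that the article's provision for skewed data is kept.
3. Delete the significance trigger and the between-arm baseline tests, and report baseline data descriptively.
4. If an unadjusted comparison is kept, label it a sensitivity analysis and state that the adjusted estimate governs the conclusion.

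The cost is wording and a few degrees of freedom. T25FW is measured at baseline and EDSS at eligibility screening, so no new data are needed. The article lists the trial as recruiting; the change should be made and dated before outcome data are compared by arm.
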